### Trial status and time plan of the study

The protocol has the version number 1, dated 26th October 2021, the recruitment began in April 2021 and will probably be completed by October 2023 (The study is being extended due to the COVID-19 pandemic). Participant follow-up and data collection will continue for 3 months after recruitment. For the subsequent data analysis, 5 months are calculated. Thereafter, we will write up and publish peer-reviewed articles.

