### Study setting

The study will be conducted at the Orthopaedic Department of Regensburg University Center, Asklepios Klinikum Bad Abbach, Germany. Here, about 18,000 patients are treated per year in the university outpatient clinic and > 1500 endoprosthetic procedures on the hip and knee joints are performed annually. Participants are recruited at the university outpatient clinic if they have a diagnosis of primary hip or knee osteoarthritis and an indication for THA or TKA. Preoperative interventions will be provided after randomization in written form or by telephone by the research nurse and/or geriatrician to the patient/family doctor/specialist. Pre-op exams and interventions can also be performed on-site at the university outpatient clinic. After surgery, the patients in the intervention group are treated in a special orthogeriatric ward (SOG unit) and the patients in the control group are treated in an ordinary orthopaedic ward of the orthopaedic university hospital.

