### Eligibility criteria

Patients (or a representative) must provide written, informed consent before any study procedures occur. Included participants should fulfil the following inclusion criteria: primary hip or knee osteoarthritis, an age ≥ 70 years and multimorbidity or an age ≥ 80 years, with an indication for elective unilateral hip or knee replacement. The waiting time until surgery must be at least 4–6 weeks. Exclusion criteria: Age < 70 years, previous bony surgery or tumour in the area of the joint to be treated, acute infection and increased need for care (care level ≥ 4).

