### Recruitment strategy

After the orthopaedic surgeons have assessed the patients referred for hip or knee problems in the university outpatient clinic and have given the indication for elective primary THA or TKA, the patient is presented to the research assistant and the geriatrician after checking the eligibility criteria. There will be a detailed explanation of the study with written informed consent. The research assistant assists the geriatrician in reviewing comorbidities and polypharmacy, and in conducting the Identification of Seniors at Risk (ISAR) screening [25], SOG screening and Nutritional Risk Screening (NRS) [26]. There is also a physical examination by the geriatrician and a laboratory test. Clinic administrators assign patients a surgery date in 4–6 weeks at the earliest or place patients on the surgery waiting list and assign them a surgery date later.

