### Randomization and consent

If the eligibility criteria are met, the patient has signed the information and consent form and the date for the surgery has been set, the participants will be randomized into the intervention or control group (usual care group). The random allocation sequence is performed computer-aided using a professional online tool for randomized clinical trials called “Randomizer” (https://www.randomizer.at/, Randomizer Version 2.1.0, Institute for Medical Informatics, Statistics and Documentation, Medical University of Graz). To ensure a balanced allocation sequence, a stratified permuted block randomization with stratification by gender (female or male) and type of care (knee or hip) will be used. We do not stratify by age, as only geriatric patients are included into the trial (age ≥ 70). The block sizes will not be disclosed, to ensure concealment. Thus, randomization will be conducted without any influence of the principal investigators, physicians, therapists, statisticians, or the research assistant.

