### Primary outcome

*Short Physical Performance Battery (SPPB)* is a measure of physical functioning [30]. SPPB evaluates balance, mobility and muscle strength by examining an individual’s ability to stand in different positions, time to walk 4 m, and time to rise up from and sit down on a chair 5 times [30]. The tests are scored between 0 and 4, leaving a maximum score of 12 [30]. The SPPB is performed preoperatively on admission to hospital, on the 3rd day after surgery, on the 7th day after surgery before discharge from hospital, and at 4–6 weeks and 3 months after surgery.

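### The time plan ends data collection 3 months after recruitment, but the last SPPB falls 3 months after a surgery that itself comes at least 4–6 weeks after recruitment

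*Protocol article*

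**What the plan says.** All sections named here are in the protocol article.

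- **Trial status and time plan of the study:** "the recruitment began in April 2021 and will probably be completed by October 2023", and then "Participant follow-up and data collection will continue for 3 months after recruitment". Five months of analysis follow.
- **Eligibility criteria:** "The waiting time until surgery must be at least 4–6 weeks".
- **Recruitment strategy:** "Clinic administrators assign patients a surgery date in 4–6 weeks at the earliest or place patients on the surgery waiting list", in which case the date comes later. No upper limit is given.
- **Randomization and consent:** allocation takes place once "the patient has signed the information and consent form and the date for the surgery has been set, the participants will be randomized", so it comes before surgery.
- **Study setting:** patients are recruited at the outpatient clinic, and "Preoperative interventions will be provided after randomization in written form or by telephone". The gap before surgery is part of the design, because part of the intervention is delivered in it.
- **Primary outcome:** the last postoperative SPPB measurements are "on the 7th day after surgery before discharge from hospital, and at 4–6 weeks and 3 months after surgery". The primary objective names the same time points.

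**The concern.** The two clocks start at different events. The visit schedule counts from surgery, while the time plan counts from recruitment and allows only the length of the postoperative follow-up. The preoperative wait has been left out.

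If the time plan were followed as written, the patients recruited last would reach the end of data collection before their 3-month visit. That visit is the latest time point of the primary outcome. The values would be missing for an administrative reason and would fall under the general provision in Data analysis for completing missing data, for example by multiple imputation, although they could simply be measured. The sample size has almost no slack to absorb extra loss: 310 × 0.9 = 279 evaluable patients, against 278 required.

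**Working it through.** **Sample size, reproduced first.** Inputs from Sample size: difference 0.5, SD 1.48, power 80%, 5% level (two-sided assumed), 1:1 allocation, 10% dropout.

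- Standardised difference: 0.5 / 1.48 = 0.338.
- Two-sample t-test: 138.5 per group, rounded up to 139, as stated.
- With dropout: 139 / 0.9 = 154.4, rounded up to 155 per group, or 310 in total, as stated.

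The sample size is therefore correct. The 3-month window is the figure that does not reproduce.

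**Length of data collection needed after the last recruitment.**

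Time needed = wait to surgery + 3 months.

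- At 4.345 weeks per month, the minimum wait is 4 / 4.345 = 0.92 to 6 / 4.345 = 1.38 months.
- Time needed: 3.9 to 4.4 months, roughly 4 to 4.5, against 3 stated. It is longer for patients on the waiting list.

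**In calendar terms**, with the last patient recruited on 31 October 2023 and 3 months taken as 91 days:

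| Wait | Surgery | 3-month SPPB | Stated end | Short by |
|---|---|---|---|---|
| 4 weeks | 28 Nov 2023 | 27 Feb 2024 | 31 Jan 2024 | 27 days |
| 6 weeks | 12 Dec 2023 | 12 Mar 2024 | 31 Jan 2024 | 41 days |

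At the stated end this patient is about 7 to 9 weeks after surgery. Day 3, day 7 and the 4–6 week visit have been reached; only the 3-month visit has not.

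**Patients affected.** Assume uniform accrual of 310 patients over April 2021 to October 2023 (30 to 31 months). The article does not give the accrual pattern.

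- Rate: 310 / (31 × 4.345) = 2.30 per week, or 310 / (30 × 4.345) = 2.38 per week.
- Recruited in the last 4 weeks: 9.2 to 9.5. In the last 6 weeks: 13.8 to 14.3.
- That is about 9–14 patients, or 3.0% to 4.6% of 310.

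**Power at the 3-month visit if this loss is added to the 10% dropout.** Evaluable per arm = (310 − lost) × 0.9 / 2, using the 31-month rate.

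| Wait | Lost | Evaluable per arm | Power (normal approximation) | Power (t-test) |
|---|---|---|---|---|
| As planned | 0 | 139 (required) | 80.4% | 80.1% |
| 4 weeks | 9.2 | 135.4 | 79.4% | 79.1% |
| 6 weeks | 13.8 | 133.3 | 78.8% | 78.5% |

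Removing all 14 from the evaluable patients, as if none would have dropped out anyway, gives (279 − 14) / 2 = 132.5 per arm and 78.2% to 78.5%. The range is about 78–79%.

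**Room in the overall timeline at the minimum wait.** Recruitment 30–31 months + 3.9–4.4 months + 5 months of analysis = 38.9 to 40.4 months, against 42 months (3.5 years, Study design), counted from April 2021. For recruitment ending on 31 October 2023, analysis would finish between late July and mid-August 2024, within the year given in Trial management.

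**The case against.** The strongest reply is that the sentence is loose shorthand in a short, hedged status section. It sets no database lock and no rule to stop visits. The per-patient schedule is stated consistently elsewhere as 3 months after surgery, and under Adherence to the program each participant receives written follow-up appointments during the inpatient stay. The overall timeline has room for the extra weeks, so no stated deadline forces any visit to be dropped. The mismatch would also vanish if recruitment were taken to end with the last operation.

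Most of this stands, and it limits the consequence. It does not make the duration right. The article uses recruitment for the outpatient process, which precedes surgery, and nowhere equates it with the operation.

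A reader might infer more than the document supports:

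- **That 3-month data will certainly be lost.** The article does not say that booked visits would be cancelled; the loss follows only if the time plan is applied literally.
- **That the loss uses up the dropout allowance.** Ten per cent of 310 is 31 patients; 9–14 is about 30% to 46% of that. About 28 patients (9%) would be affected with a 12-week wait, but that wait is an assumption found nowhere in the article.
- **That surgery follows randomisation by at least 4–6 weeks.** The minimum is a waiting time to surgery. A waiting-list patient is randomised only once a date is set, so the interval from randomisation to surgery is not fixed, and no number of months after the last randomisation can be derived.
- **That the trial's power as a whole is reduced.** Only one of four postoperative SPPB time points is affected, and the sample size section does not tie its calculation to the 3-month visit.

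**Conclusion.** The point holds as an internal contradiction. A data-collection window of 3 months after recruitment is at least 4–6 weeks too short for the article's own waiting time and visit schedule, and more for patients who wait longer. The visit schedule and the sample size are sound; the time plan is what needs correcting.

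The size is modest: at most 1 to 2 percentage points of power, at a single time point. The loss should be roughly balanced between arms because it depends on the recruitment date, so precision is at stake more than bias. These figures rest on a literal reading of the time plan, uniform accrual and the minimum wait. The correction is worth making because the affected visit is the latest measurement of the primary outcome and the remedy costs almost nothing.

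**What to change.** In the time plan, replace the sentence on the end of follow-up with: *Follow-up and data collection continue until the last randomised patient has completed the visit 3 months after surgery.* Start the 5-month analysis period from that point.

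This wording ties the end of the study to surgery and needs no assumption about the wait or about the interval from randomisation.

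The cost is a database close about 4–6 weeks later than now implied, or more if late recruits come from the waiting list. No change to the visits, the sample size or the analysis is needed. Because the article gives no maximum wait, the sponsor should check the actual waiting times of the last recruits against the 3.5-year limit.

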## Data Availability

Dissemination strategies include reports, the presentation of results in peer-reviewed journals and at conferences, and public relations activities in line with the recommendations of the International Committee of Medical Journal Editors (ICMJE). Due to data protection restrictions and regulations only the University of Regensburg and the Technical University of Munich will have access to the full dataset. The datasets generated and/or analysed during the current study are available on reasonable request due to privacy or other restrictions.

## Abbreviations

ADL: Activities of daily living
ALT: Alanine aminotransferase
API: Appropriate preoperative intervention
AST: Aspartate aminotransferase
BUN: Blood urea nitrogen
CBC: Complete blood count
CGA: Comprehensive geriatric assessment
Cr: Creatinine
Ccr: Creatinine clearance
CRP: C-reactive protein
EQ-5D: Euroquol Quality of Life Index
GDS: Geriatric Depression Scale
GGT: Gamma glutamyltransferase
HbA1c: Glycosylated hemoglobin A
IADL: Instrumental activities of daily living
INR: International normalized ratio
ISAR: Identification of Seniors at Risk
MMSE: Mini Mental State Examination
MRC: Medical Research Council
NRS: Nutritional Risk Screening
NU-DESC: Nursing Delirium Screening Scale
OA: Osteoarthritis
OGC: Orthogeriatric co-management
PBM: Patient Blood Management
POPS: Perioperative Care of Older Persons
PREM: Patient-reported experience measures
PROM: Patient-reported outcome measures
PTT: Partial thromboplastin time
RCT: Randomized controlled trial
RiFLS: Risk Factor Liaison Service
SPPB: Short Physical Performance Battery
SOG: Special orthopaedic geriatrics
THA: Total hip arthroplasty
TKA: Total knee arthroplasty
TSH: Thyroid-stimulating hormone
TUM: Technical University of Munich
UN: United Nations
WOMAC: Western Ontario and McMaster Universities Osteoarthritis Index
